# A multicentre, randomised intervention study of the Paediatric Early Warning Score: study protocol for a randomised controlled trial

**DOI:** 10.1186/s13063-017-2011-7

**Published:** 2017-06-08

**Keywords:** Paediatric Early Warning Score, Randomised controlled trial, Paediatrics, Intensive care unit

## Abstract

**Background:**

Patients’ evolving critical illness can be predicted and prevented. However, failure to identify the signs of critical illness and subsequent lack of appropriate action for patients developing acute and critical illness remain a problem. Challenges in assessing whether a child is critically ill may be due to children’s often uncharacteristic symptoms of serious illness. Children may seem relatively unaffected until shortly before circulatory and respiratory failure and cardiac arrest.

The Bedside Paediatric Early Warning Score has been validated in a large multinational study and is used in two regions in Denmark. However, healthcare professionals experience difficulties in relation to measuring blood pressure and to the lack of assessment of children’s level of consciousness. In addition, is it noteworthy that in 23,288-hour studies, all seven items of the Bedside Paediatric Early Warning Score were recorded in only 5.1% of patients.

This trial aims to compare two Paediatric Early Warning Score (PEWS) models to identify the better model for identifying acutely and critically ill children. The hypothesis is that the Central Denmark Region PEWS model is superior to the Bedside PEWS in terms of reducing unplanned transfers to intensive care or transfers from regional hospitals to the university hospital among already hospitalised children.

**Methods/design:**

This is a multicentre, randomised, controlled clinical trial where children are allocated to one of two different PEWS models. The study involves all paediatric departments and one emergency department in the Central Denmark Region. The primary outcome is unplanned transfer to the paediatric intensive care unit or transfer from regional hospitals to the university hospital. Based on preliminary data, 14,000 children should be included to gain a power of 80% (with a 5% significance level) and to detect a clinically significant difference of 30% of unplanned transfers to intensive care or from regional hospitals to the paediatric department at the university department. A safety interim analysis will be performed after inclusion of 7000 patients.

**Discussion:**

This is the first randomised trial to investigate two different PEWS models. This study demonstrates the safety and effectiveness of a new PEWS model and contributes to knowledge of hospitalised children’s clinical deterioration.

**Trial registration:**

ClinicalTrials.gov, NCT02433327. Registered on 27 April 2015.

**Electronic supplementary material:**

The online version of this article (doi:10.1186/s13063-017-2011-7) contains supplementary material, which is available to authorized users.

## Background

Patients’ evolving critical illness and death can be predicted and prevented [1, 2]. The clinical deterioration of hospitalised patients is often preceded by physiological changes up to 24 hours before death [2, 3]. The care and treatment of critically ill children is a particular challenge, as children’s symptoms of critical illness can be uncharacteristic. A child with sepsis or severe dehydration can seem relatively unaffected, and the acute condition is often only identified by the affected vital parameters [4]. Children’s compensatory mechanisms are better than those of adults because they are able to maintain an almost normal blood pressure despite considerable loss of fluid. On the other hand, a child’s condition can deteriorate almost immediately when his/her ability to compensate is overwhelmed. Thus, it is important to identify and act on the often subtle signs of acute and critical illness in a child, as the prognosis for survival if a child develops cardiac arrest is very poor [5]. International studies have shown that between 8% and 14% of cardiac arrest incidences in intensive care units involve paediatric patients [6]. The rate of survival is only between 15% and 33%, with subsequent very poor neurological outcomes in 35% of those who survive [7]. A study of 126 deaths among English children showed that 89 deaths occurred in hospital; among them, 63 (71%) could have been avoided [8]. The difficulty of recognising the severity of the disease was a decisive factor, as was the inability to measure and interpret physical signs correctly. To provide timely care and treatment for children, systematic assessment of children’s symptoms and their severity is vital. If health professionals do not systematically observe, interpret and act adequately to address changes in a child’s condition, a hospitalised child is likely to experience serious consequences [8]. The Paediatric Early Warning Score (PEWS) is a system for identifying clinically deteriorating children. The PEWS tool is a simple physiological scoring system that can be applied at the patient’s bedside using parameters that can easily be measured without complex, expensive equipment.

The Canadian Bedside PEWS model has proven to be at least equally good as if not superior to other paediatric early warning system models, with a sensitivity of 83% and a specificity of 95% [9–11]. The model has been developed, tested and modified and now comprises seven different parameters. However, it includes the measurement of blood pressure, which is a specific challenge in the paediatric population. Children are often upset when their blood pressure is measured, which either causes the pressure to increase (not necessarily a sign of clinical exacerbation of disease) or results in failure to obtain blood pressure measurements. At the same time, low blood pressure is a late indicator in connection with evolving critical illness due to children’s ability to compensate; this could be an argument for not measuring the blood pressure of all hospitalised children [5]. Moreover, the model does not include the assessment of children’s level of consciousness, which is an important factor for assessing whether critical illness is evolving in children. Finally, note that all seven items were recorded in only 5.1% of patients in 23,288-hour studies [11].

In the present study, we compare the Canadian model with the Central Denmark Region model, which includes the assessment of the level of consciousness, but not the measurement of blood pressure. Blood pressure measurement in the Central Denmark Region model will be performed as an additional optional measurement in line with other additional measurements such as urine output. It could be relevant among children with a high PEWS value, i.e. children at risk of evolving critical illness or children whose illness requires blood pressure measurement. Blood pressure measurement will thus be a prescribed action and will not be used as a screening mechanism for all hospitalised children as in the Bedside PEWS model. Apart from this, the two PEWS models are similar in terms of their underlying action algorithms, age categories and cut-off values for vital signs.

This manuscript is prepared according to the Standard Protocol Items: Recommendations for Interventional Trials (SPIRIT) guidelines [12].

### Objective

The aim of this study was to compare the ability of the two PEWS models to reduce the number of unplanned admissions to intensive care or the number of transfers from regional hospitals to the university hospital among already hospitalised children due to clinical deterioration.

### Hypothesis

The hypothesis is that the Central Denmark Region PEWS is superior to the Bedside PEWS in terms of reducing hospitalised children’s unplanned transfers to the intensive care unit and transfers from regional hospitals to the university hospital due to clinical deterioration requiring proximity to a paediatric intensive care unit (PICU).

### Trial design

This is a multicentre, randomised, controlled clinical intervention study.

## Methods/design

### Study setting

The study is ongoing in four paediatric departments, four paediatric emergency and assessment units, one emergency department and a specialised paediatric unit for children with neurological illness in the Central Denmark Region. Including both a university hospital and several regional hospitals helps ensure the highest possible diversity in the population and strengthens the study’s generalisability. The participating departments are listed on the project homepage (www.pews.dk). None of the participating hospitals had been working with any kind of PEWS model prior to this study.

### Eligibility criteria

Participants are aged 18 years and below.

Inclusion criteria are as follows:All children admitted to the participating departmentsAll children examined at the acute paediatric assessment units in the Central Denmark Region

Exclusion criteria are as follows:Children admitted directly to neonatal wardsChildren admitted directly to intensive care unitsChildren dead upon arrival at the hospitalChildren admitted due to social interaction problemsChildren receiving palliative careChildren whose informed consent was not obtained

### Interventions

Both of the PEWS tools in this project consist of seven parameters (Table 1). Each individual parameter generates a score of 0, 1, 2 or 4; these are accumulated to a total score. See Additional file 1 for a more detailed a description of the scoring systems.

**Table 1 Tab1:** Contents of the two PEWS models

Bedside PEWS model	Central Denmark Region model
Heart rate	Heart rate
Respiratory rate	Respiratory rate
Respiratory effort	Respiratory effort
Systolic blood pressure	Level of consciousness
Pulse oximetry	Pulse oximetry
Oxygen therapy	Oxygen therapy
Capillary refill time	Capillary refill time

The two PEWS models investigated in the present study are incorporated into a management system that consists of the following elements:An electronic patient chart with unique software that provides an age-specific sub-score for each of the seven clinical observations and an accumulated total PEWS valueAn action algorithm providing a set of minimal actions to assist deteriorating children by involving all necessary team members in a timely manner; the algorithm also assists in determining the level of necessary care (see Table *2*)

**Table 2 Tab2:** Decision algorithm for both PEWS models

PEWS value	Minimum observation interval	Decision algorithm
0	Every 12 hours	Continue scoring every 12 hours
1–2	Every 6 hours	Nursing staff ABCDE optimizes; see action card (shown in Additional file 2)
		If the score is 2, inform the nurse in charge and as a minimum, for one single score at 2, inform the nurse in charge before the physician
3–5	Every 4 hours	Nursing staff ABCDE optimizes; see action card
		If the score is 3 or above or as a minimum For one single score at 3, inform the physician. The physician is to make a plan of action
6	Every 2 hours	Nursing staff ABCDE optimizes; see action card
		Send for the physician
		The physician shall attend to the patient and make a plan of action. Any indication for taking blood pressure?
7–8	Every hour	Nursing staff ABCDE optimizes; see action card
		Send for the physician
		The physician shall attend to the patient within 30 minutes
		The physician confers with the specialist doctor
		The physician makes a plan of action. Any indication for taking blood pressure?
9 or above	Every 15 minutes	Nursing staff ABCDE optimizes; see action card
		The physician shall attend to the patient within 15 minutes
		The physician confers with the specialist doctor
		The physician makes a plan of action

*ABCDE* Airway, Breathing, Circulation, Disability, ExposureClinical guidelinesEducational programme for nurses and medical doctors

All nurses employed in the participating departments attended a 2-hour teaching session prior to implementing the PEWS system, while medical doctors attended a 30-minute teaching session. The children included in the study will be monitored using one of the two different PEWS models. Both models include the measurement of vital signs at different intervals according to the child’s condition. The PEWS will be measured on admission; action then follows as guided by the algorithm. If a child’s clinical condition is deteriorating, the ‘score’ for the observations will increase; a higher or increasing score gives an early indication that intervention may be required. Based on the results of the clinical assessment and PEWS value, nurses can find the corresponding action(s) on the PEWS action algorithm. The corresponding action could, for example, be more frequent reassessment or notifying the charge nurse or paediatrician.

Observations are documented in the electronic patient chart, which also provides information based on the PEWS value for observation intervals. Underlying both PEWS tools are algorithms of clinical decision support for the critically ill child based on the Airway, Breathing, Circulation, Disability, Exposure (ABCDE) principle (see Additional file 2), clinical guidelines and guidance for standardised monitoring.

### Outcomes

The primary outcome is the sum of unplanned transfers to the PICU and transfers from regional hospitals to the university hospital or the number of deaths. Transfers from regional hospitals to the paediatric department at the university hospital are equated with transfers to the PICU; children who need intensive care at the regional hospitals will be transferred to the paediatric department at the university hospital to ensure proximity to the PICU.

The secondary outcomes are as follows:Paediatric Index of Mortality scoreSeverity of illness during PICU stay based on invasive ventilation and inotropesLength of hospital stayLength of PICU stay

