#### Paediatric Index of Mortality

The Paediatric Index of Mortality (PIM3) is used to provide an estimate of mortality risk among children admitted to paediatric intensive care [13]. The PIM3 consists of 10 variables that should be collected within one hour after arrival at the PICU. The PIM3 score consists of physiological variables and categorical variables that classify patients based on the reason for admission, the use of mechanical ventilation and diagnostic risk data [13]. It is not meant to be used as a marker for the severity of illness of individual patients; however, like other mortality prediction models, it has been used to evaluate the risk of mortality when registering patients in clinical trials and as a tool for monitoring the quality of intensive care [13]. Thus, we also use invasive ventilation and inotropes as markers for the severity of illness.

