**Fig. 2 Fig2:**
[figure not shown]
SPIRIT study schedule

Separate interactive registration modules in the electronic patient chart were designed for each of the two PEWS models. The study data are extracted from the electronic patient charts. Thus, healthcare professionals in each department are responsible for data collection and data entry into the electronic patient chart as well as for obtaining consent from the parents.

For each patient included in the study, the following data are collected:Baseline demographics: child’s age, gender, pre-existing conditions, diagnostic category (cardiac, post-surgical, neurological, respiratory, infection, hydration)Clinical characteristics: discharge diagnosis, triage level at admission, time of day of critical event (day, evening, night)PEWS parameters and temperature in the 24 hours preceding transfer to the PICU, ending one hour before transfer to the PICUFrequency of PEWS and temperature measurements during the last 24 hours prior to transfer to the PICU, ending one hour before transfer to the PICUData from PICU: PIM3 scoreOutcome data: unplanned transfer to the PICU or university hospital, length of hospital stay, length of PICU stay

Transfers to the PICU and transfers from regional hospitals to the university hospital will be identified from the electronic patient charts. Two researchers will review each of these medical records to exclude planned transfers. These are transfers that are elective or planned in advance, transfers coming directly from the operating room and transfers in which the need for PICU care was due to the need to recover from sedation.

This trial will follow the recommendations from the Consolidated Standards of Reporting Trials (CONSORT) statement for non-pharmacological treatment interventions.

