### Statistical methods

Statistical analysis will follow the modified intention-to-treat principle [14]. Analysing the primary outcome, logistic regression of PEWS on unplanned PICU admissions will be performed to determine odds ratios (ORs) and 95% confidence intervals (CIs). The analysis will be adjusted for age. In the secondary outcome analysis, categorical data will be analysed using the chi-square test. Continuous data that are not normally distributed will be analysed using the Mann-Whitney *U* test. A *p* value <0.05 is considered significant.The two PEWS tools will also be evaluated using sensitivity, specificity and the receiver operating characteristic curve. In this study, sensitivity is the ability of the PEWS tool to correctly identify children at risk of an unplanned transfer to the PICU. Specificity is the ability of the tool to demonstrate a low score among children who are not at risk of an unplanned transfer to the PICU; thus, a low specificity indicates a high rate of false positives. Sensitivity and specificity will be calculated to measure the validity of the tools and the most predictive score for an unplanned transfer to the PICU. As the PEWS must be able to identify children at risk of acute life-threatening conditions and provide a ‘window’ for intervention, data analysis will stop one hour prior to the occurrence of the acute life-threatening condition to avoid overestimating the effect of the PEWS.

Descriptive statistics will be calculated to describe baseline variables and clinical characteristics. The descriptive analysis will be summarised as percentages, with median and interquartile ranges provided for continuous variables. STATA version 10 will be used for the analyses.

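### Three secondary outcomes are defined on PICU admission, which the tools are meant to change, so testing them among admitted children is open to selection bias of unknown direction

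*Protocol article*

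**What the plan says.** The Outcomes section of the protocol article lists four secondary outcomes: PIM3, severity of "illness during PICU stay based on invasive ventilation and" inotropes, length of hospital stay, and length of PICU stay. All but length of hospital stay depend on a PICU admission. The Paediatric Index of Mortality section describes PIM3 as giving an "estimate of mortality risk among children admitted to paediatric intensive care", from variables "collected within one hour after arrival at the PICU". Data collection and management lists "length of hospital stay, length of PICU stay" among the outcome data and states no value for a child who never enters the PICU.

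PICU admission is itself part of the primary endpoint: "The primary outcome is the sum of unplanned transfers to the PICU and transfers from regional hospitals to the university hospital", or deaths. The Hypothesis section expects the new tool to reduce "unplanned transfers to the intensive care unit and transfers from regional hospitals to the university hospital due to clinical deterioration", and Sample size puts the expected reduction at 30%.

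On analysis, Statistical methods says: "In the secondary outcome analysis, categorical data will be analysed using the chi-square test". Continuous data that are not normally distributed get the Mann-Whitney test, with significance at p<0.05. The principle is modified intention-to-treat. The section names no denominator for the PICU-based outcomes and gives no caveat about comparing admitted children only.

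**The concern.** Randomisation makes the two arms comparable as randomised. It does not make the children who later reach the PICU comparable if the tools influence who gets there, and that influence is the trial's own hypothesis. A tool that averts milder transfers leaves a sicker PICU group. A tool that prompts earlier transfer, or keeps the worst cases out, leaves a milder one. In either case a difference in PIM3, ventilation or PICU stay can appear although no child's illness has changed.

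The problem is greatest when the primary result is positive, because the two PICU groups have then most likely been selected differently. A reader would naturally look to these outcomes to interpret a fall in transfers, and a tool that works could seem to make PICU children sicker. Restricting to admitted children also drops those who die before reaching the PICU. It drops, too, those moved to the university paediatric department who never enter the PICU. Yet Outcomes counts deaths in the primary endpoint and equates those transfers with PICU transfers.

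**Working it through.** **Inputs.** From Sample size: 154 unplanned PICU transfers in 10,000 admissions, and a 30% expected reduction. From the Abstract and Allocation: 14,000 children, 1:1, so 7000 per arm. The article gives no size for the PICU-based outcomes, so there is no stated figure to reproduce for them. (The 7112 per group in Sample size does not follow from its own inputs: a two-sided, pooled-variance calculation gives 9500. That is a separate matter, and only the rates are used here.)

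**Step 1. How many children enter these tests.**
- Control rate: 154/10,000 = 1.54%. With a 30% reduction: 1.54% × 0.70 = 1.078%.
- Admissions: 7000 × 0.0154 = 107.8 and 7000 × 0.01078 = 75.5.
- Share of all randomised: (107.8 + 75.5)/14,000 = 1.3%.

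**Step 2. What selection does to a severity score.** Let u be the severity percentile among children who would be admitted under the control tool, uniform from 0 (mildest) to 1, with the same distribution in both arms. The new tool averts a child at u with probability a(u), averaging 0.30. No child is made sicker. The probability that an admitted child on the new tool is sicker than an admitted control child is

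P = ∫u(1 − a(u))du / ∫(1 − a(u))du, where 0.50 means no bias.

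The rejection rates come from simulating the two-sided 5% Mann-Whitney test with about 108 versus 75 children. Ranges cover slightly different ways of drawing the counts.

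| Assumed pattern of averted transfers | P | Rejection |
|---|---|---|
| Random 30% | 0.50 | 4–5% |
| Weak sorting: 40% of the milder half, 20% of the rest | (0.30×0.25 + 0.40×0.75)/0.70 = 0.54 | 13–14% |
| Mixed: 65% of the mildest 30%, 15% of the rest | (0.105×0.15 + 0.595×0.65)/0.70 = 0.575 | 40–42% |
| Exactly the mildest 30% | midpoint of 0.30 to 1 = 0.65 | 91–95% |
| Exactly the most severe 30% | midpoint of 0 to 0.70 = 0.35 | about 95%, opposite direction |

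**Step 3. Ventilation as a yes/no outcome.** Suppose a share v of control admissions is ventilated (assumed) and only non-ventilated admissions are averted. The share among admitted children on the new tool becomes v/0.70: 0.20/0.70 = 29%, 0.30/0.70 = 43%, 0.50/0.70 = 71%. The chi-square test among admitted children then rejects in about 27%, 43% and 84% of trials. Over all randomised children the ventilated proportion is the same in both arms; for v = 0.30 it is 0.30 × 1.54% = 0.46%. This is again complete sorting, so these are upper-end figures.

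**Step 4. Sensitivity to the inputs.** A perfectly sorted reduction of 10% instead of 30% gives about 25% rejection. If only half of the 154 events were true PICU admissions (assumed; about 54 control children), the extreme case falls to about 67% and the mixed case to about 25%.

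**The case against.** **The denominator is inferred.** Statistical methods names tests and does not restrict them to admitted children. A chi-square test of ventilation or inotropes over all randomised children would fit its wording, and analysis sets are often left to an analysis plan, which is not shown. This stands for ventilation/inotropes and PICU days, although defining severity within the PICU stay makes the restricted reading the natural one. It does not help PIM3, which has no value without an admission.

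**Bias is possible, not established.** A reader might infer that these tests are biased. The documents do not support that. Bias needs the tools to change which children are admitted, and the Background says the two models share action algorithms, age categories and cut-offs. Table 1 shows one parameter of seven exchanged. If averted transfers are a random subset, there is no bias. This objection stands and sets the wording of the point.

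**The large figures are worst cases.** The 91–95% requires the full 30% reduction and perfect sorting. The 108 is also uncertain: Sample size calls the events PICU transfers, whereas the Abstract links the preliminary data to a target that includes regional-to-university transfers. This stands; the weak and mixed scenarios are the more useful guide.

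**Two further inferences should be resisted.** A reader might conclude that ventilation and inotropes are not collected, because the list under Data collection and management gives only PIM3 as PICU data. That list is condensed, and both Outcomes and the Paediatric Index of Mortality section say the markers are used. A reader might also cite the caution on PIM3, "It is not meant to be used as a marker for the severity of illness of individual patients". It concerns individual patients, not conditioning on admission, and the article answers it by adding ventilation and inotropes.

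**Conclusion.** The point holds as a matter of design. Three secondary outcomes are defined on a post-randomisation event that belongs to the primary endpoint, and the plan gives them ordinary two-group tests. On the natural reading, those tests are open to selection bias whose direction cannot be known in advance. In the assumed scenarios with a 30% reduction, a nominal 5% test rejects in anything from about 5% of trials (random subset) through 14% and 40% to 91–95% (perfect sorting of the mildest), with no child made sicker. The top of that range should not be read as an expected error rate. Modified intention-to-treat does not repair a comparison made within a subset that the outcome selects. The outcomes are secondary, so the primary comparison is unaffected; what is at risk is the interpretation placed on it.

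**What to change.** Analyse two outcomes by arm as randomised, over all randomised children:

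- **(a)** Yes/no: unplanned PICU admission with invasive ventilation or inotropes, or death. Including death prevents a child who dies on the ward from being coded as a good outcome.
- **(b)** PICU days, with 0 for children not admitted and a stated rule for deaths before the PICU, for example worst rank.

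Report PIM3 and length of PICU stay among admitted children by arm as description only, without a between-arm test, and say that admission may have been selected differently in the two arms.

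The cost is wording in the analysis plan. Recruitment, randomisation and care do not change, so this was still feasible with 12,000 children already randomised. The ventilation and inotrope data are needed for the outcome already planned. Statistically, both new outcomes have many zeros and modest precision. PICU days over all children mix how often children are admitted with how long they stay, so they partly repeat the primary outcome and answer a different question from length of stay among admitted children.
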